### Representativeness of the sample and sample selection (at cluster level)

In 2003, the Sigmund Freud Institute carried out a baseline survey of all Frankfurt daycare centers (114 centers with approximately 5,300 children, aged 3 to 4). Children’s aggressiveness, hyperactivity and anxiety were measured using the teachers’ ‘observation questionnaire for preschool children’ [46]. Additionally, the SES of all daycare centers was assessed, operationalized as the family’s dependency on financial support by the Frankfurt Municipality that paid the monthly fee for the daycare center indicating low SES. These data were stratified by aggressiveness, hyperactivity, anxiety and SES and resulted in the division of 114 daycare centers into 10 clusters (see Table 1). EVA daycare centers were randomly chosen out of the clusters’ groups with low SES. (Note: here we are considering clusters on a higher level, each cluster contains several daycare centers).

### Control for neighborhood community risk (at cluster level)

To prove that our sample comprises children at risk with low SES, we additionally charted data from the Frankfurt Municipality Statistics about childhood poverty in Frankfurt’s urban districts operationalized as the children’s dependency on social welfare (in German: Sozialgeld, SGB II-Leistungsbezug, [47]). In 2009 about 20,242 children in Frankfurt under the age of 15 were on social welfare. Between the different urban districts, there are large disparities in the percentage of these children. There were districts where the percentage lay under 5% (for example, ‘West end’), which are colored in Figure 2 in a light gray, but there are other districts, where over 40% of the children were on social welfare (for example, ‘Gallus’). These quarters are colored in dark gray in Figure 2[47]. The correlation coefficient of social welfare and the unemployment rate of the parents was found to be *r* = 0.89 [47]. This high correlation hints at the cumulative geographic concentration of social problems of children in particular urban districts. The EVA daycare centers are located in these special quarters (see Figure 2).

**Figure 2 F2:**
[figure not shown]
**Distribution of social welfare child beneficiaries in Frankfurt’s urban districts and position of ‘Evaluation of two prevention programs ‘Early Steps’ and ‘Faustlos’ in daycare centers with children at risk’ (EVA) study daycare centers.** Source: Jacobs [47].

### Randomization

As Figure 1 shows, randomization was performed at cluster level. Our statistician (TF), uninformed about the identity of the daycare centers, used a table of random numbers for randomizing the 14 daycare centers. Individual participants (children and their parents, as well as daycare teachers) were aware of their group assignment, that is, if they were participating in the Early Steps intervention or the Faustlos control group.

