#### Individual level (children)

In all selected daycare centers, all of the children, male and female, between 3 years 0 months and 4 years 11 months of age at the time of recruitment and their parents were approached to participate in our program. We excluded children beyond the age range. Other exclusion criteria were not applied at the individual level.

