### Design

The study is performed as a cluster-randomized controlled trial over the course of 3 years. The randomization clusters are represented by public daycare centers in the city of Frankfurt am Main, Germany that were assessed before being randomized. Figure 1 summarizes the study design.

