### Ethical issues

The Ethic Review Commission of the Federal Chamber of Child and Adolescent Psychotherapists of the State of Hessen, Germany, have approved the final study protocol and the final version of the written informed consent form. Written consent was obtained from each participating family.

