### Status of the study

Ongoing recruitment.

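### At least some families appear to be recruited after their center's arm is known, so consent may differ by arm; the article does not fix the order of consent, t0 assessment, randomization and disclosure

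*Protocol article*

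**What the plan says.** All statements are in the protocol article.

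- **Randomization.** In the past tense, the statistician, who did not know which centers they were, "used a table of random numbers for randomizing the 14 daycare centers". The same section says "Individual participants (children and their parents, as well as daycare teachers) were aware of their group assignment".
- **Status of the study.** The whole entry is "Ongoing recruitment".
- **Individual level (children).** All children in the age range "at the time of recruitment and their parents were approached to participate in our program". Beyond age, "Other exclusion criteria were not applied at the individual level".
- **Ethical issues.** "Written consent was obtained from each participating family".
- **Design.** The clusters are public daycare centers "that were assessed before being randomized".
- **Planned analyses for the primary outcome.** The analysis follows intention to treat. Baseline characteristics are described at individual and cluster level, and covariates enter only where judged relevant.

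**The concern.** In a cluster trial, randomizing centers balances the populations that the centers serve. It balances the enrolled children only if enrolment does not depend on the arm. When families decide after the arm is known, the decision itself can differ by arm.

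The two offers differ enough to make this plausible. According to the intervention sections, Early Steps brings weekly on-site counseling and, in individual cases, therapy for child and parents; Faustlos is a 28-lesson curriculum. The Discussion says that several Early Steps modules are aimed at children at risk, including those with disorganized attachment. Families may thus have an arm-specific reason to sign up, and that reason is related to the primary outcome, MCAST attachment representation.

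At stake are the baseline comparability of the arms on MCAST and on family risk that is not measured. Intention to treat keeps enrolled children in their assigned arm but has no bearing on who was enrolled.

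**Working it through.** **1. The order of events, section by section.**

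- *What is still being recruited?* Power analysis asks for seven centers per treatment, and Randomization reports all 14 as randomized. Open recruitment can therefore hardly mean centers; children and families remain.
- *Is the arm known?* Randomization says that families and teachers know it. It does not say whether they learned it before or after consent.
- *Is entry a family decision?* Yes, by Ethical issues. Individual level (children) ties eligibility to age at recruitment and not to the date of allocation or disclosure.
- *Does Design settle it?* There it is the centers that are assessed before randomization. That could mean the 2003 survey, for which the section on representativeness also speaks of centers being assessed, or it could mean t0 testing. On the first reading it says nothing about consent. On the second it covers the children tested by then, but not those recruited later.

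Taken together, at least some families appear to be recruited with the arm known. This is an inference, because no section states the order.

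**2. The plan's own sample size, reproduced to obtain a standard error.** The inputs, from Power analysis, are d = 0.5, α = 0.05 (two-sided reproduces the stated n), power 0.80, CV = 0.467, ICC = 0.0465, m = 20 or 17, and 7 centers per arm.

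- Unclustered n per arm = 2(1.96 + 0.8416)² / 0.5² = 62.79, rounded up to 63, as stated.
- Design effect DE = 1 + [(1 + CV²)m − 1] × ICC.
  - m = 20: 2.0863; × 63 = 131.44; / 20 = 6.57 centers, as stated.
  - m = 17: 1.9164; × 63 = 120.73; / 17 = 7.10 centers, as stated.
- Standard error of the arm difference in SD units = √(2·DE / 7m): 0.173 for m = 20 and 0.179 for m = 17.

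These figures do not test the order of events. They only give a scale.

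**3. What a selection shift would do (assumed range).** With no true effect and a spurious shift b in the analysed outcome, the rejection probability is 1 − Φ(1.96 − b/SE) + Φ(−1.96 − b/SE), by normal approximation.

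| Shift b (SD) | m = 20 | m = 17 |
|---|---|---|
| 0 | 5.0% | 5.0% |
| 0.1 | 8.9% | 8.6% |
| 0.2 | 21.2% | 20.0% |
| 0.3 | 41.2% | 38.7% |

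**4. From consent to a baseline shift (assumed figures).** If a fraction p consents and consenters differ from non-consenters by δ SD, the enrolled mean departs from the eligible mean by δ(1 − p).

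- Same δ = 0.5 in both arms, consent 70% in Early Steps and 50% in Faustlos: 0.15 and 0.25, an arm difference of 0.10 SD. If consenters are the more troubled families, Faustlos then holds the more troubled sample.
- Consent 70% in both arms, but δ = 0.5 only in Early Steps: 0.15 and 0, a difference of 0.15 SD with the more troubled sample in Early Steps.
- Same consent and same δ: zero.

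So neither the sign nor the size can be fixed without consent data. These are also shifts in baseline level, whereas the plan's d = 0.5 rests on pre/post differences and the main analysis concerns change. They must not be read as fractions of d, or carried one for one into the table above.

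**The case against.** A reader might infer that families are recruited after randomization in full knowledge of the arm, and that center-level randomization therefore no longer protects the comparison. The documents do not support that as a stated fact. The sentence on awareness can be read as a plain blinding statement about children already enrolled. The approach to families and the obtaining of consent are both written in the past tense. Figure 1, to which Design and Randomization refer, was not available for this review and may show the order; so may the full protocol.

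Nor is protection lost altogether. All age-eligible children in the selected centers were approached with no further exclusion, so differential consent is the main route left, and its size may be zero. The plan already includes repeated-measures analysis of covariance from baseline, a baseline description and possible covariates.

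What stands of this: the order is inferred, and the size is unknown. What does not stand is that the matter is only an omission of the kind an article leaves to the full protocol. Randomization reported as done, open allocation and continuing recruitment are positive statements that need reconciling. Optional covariates and intention to treat do not remove selection on unmeasured family risk.

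**Conclusion.** The point holds as a risk that should be addressed, with medium confidence. At least some families appear to be recruited after their center's arm is known, and consent may then differ by arm. The documents give neither size nor direction for any resulting bias. The type I error figures rest on assumed shifts in the analysed outcome, the plan's ICC and CV, seven centers per arm and a normal approximation. They show that a modest bias would matter if present, not that it is present. If consent and t0 assessment did precede disclosure for every child, a sentence saying so would settle the point.

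**What to change.** 1. Reconcile Design, Randomization and Status of the study by stating the order of family consent, t0 assessment, randomization and disclosure of the arm.
2. For any center or family not yet told the arm, complete consent and t0 MCAST before disclosure.
3. Record each child's consent date against the center's disclosure date.
4. Report eligible, approached and consented counts by arm from the center rosters.
5. Make adjustment for baseline MCAST score and age a fixed part of the primary model.
6. Add a sensitivity analysis restricted to children who consented before disclosure.
7. If most consented afterwards, state that the result is open to recruitment bias.

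The cost is some extra data recording and analysis and, possibly, a more cautious conclusion. The primary analysis set is not reduced. Moving the restriction in step 6 into the primary analysis would cost power: with seven centers per arm and the formula above, power = Φ(0.5/SE − 1.96) is 79.6% at 17 children per center, about 75% at 14 and 67% at 10. It is therefore better kept as a sensitivity analysis.

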### Planned analyses for the primary outcome

#### Primary outcome: MCAST attachment representation

Data will be analyzed with respect to the intention of treatment. We will describe all baseline characteristics at the individual as well as at the cluster level. Moreover, we will assess the characteristics of any cluster and if the children drop out. Relevant characteristics will be added if applicable as covariates to the models. Children’s attachment representations are measured on MCAST’s overall attachment classification (secure vs insecure-ambivalent vs insecure-avoidant vs insecure-disorganized attachment representation) and on MCAST’s disorganization and narrative coherence scores. As the main analysis involves changes in MCAST disorganization and narrative coherence scores from the baseline and the endpoint in the intervention versus the control group, an analysis of covariance is applied with repeated measures and linear regression with autocorrelated data (compound symmetric covariance structure models). Changes in the overall attachment classifications are calculated by tests for frequency distributions and procedures of survival analysis (Cox, regression, log-rank tests). All procedures take the CRCT design into account. Therefore, variances of the sample mean will be corrected using the factor *n**/*n* (as described above).

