### Assessments

Teachers evaluate children’s behavior (aggressiveness, hyperactivity, anxiety and social competence) and well-being using the following questionnaires: before (t0 pre), after 12 months, (t1 12 mo), after intervention (t2 post) as well as 1 year after the end of intervention (t3 follow-up): the Caregiver-Teacher Report Form 1½-5 (C-TRF) [33,34], the Strengths and Difficulties Questionnaire (SDQ) [35,36] and the Positive Development and Resilience in Daycare Center’s Daily Routine (PERIK) [37,38], an observational instrument for teachers. Moreover, the Self-Reflective Functioning Scale [39,40] will be applied for the teachers. Parent’s perspective will be evaluated using the SDQ [35,36]. Children’s assessment is conducted before (t0 pre) and after intervention (t2 post), as well as 1 year after the end of intervention (t3 follow-up). Independent and trained psychologists assess children’s intelligence using the German adaptation of Wechsler Preschool and Primary Scale of Intelligence-III Assessment (HAWIVA) [41] and as well as the children’s attachment representation. The Manchester Child Attachment Story Task (MCAST) [42], a narrative story stem task that involves playing with dolls, is a validated, structured measure that evaluates young children’s attachment representations through the use of play scenarios allowing for differentiation between four overall attachment classifications: secure attachment, insecure-ambivalent attachment, insecure-avoidant attachment and insecure-disorganized attachment representations. Measures and time points of assessment are presented in Table 2.

**Table 2 T2:** Assessments

**Measure point**	**Child**	**Teacher**	**Parents**
t0 (pre-study)	MCAST, HAWIVA	C-TRF, SDQ, PERIK	SDQ
t1 (12 months)		C-TRF, SDQ, PERIK	
t2 (post study, 24 months)	MCAST, HAWIVA	C-TRF, SDQ, PERIK, SRS	SDQ, interview
t3 (follow-up, 36 months)	MCAST, HAWIVA	C-TRF, SDQ, PERIK	SDQ

*C-TRF* Teachers Report Form, *HAWIVA* Wechsler Preschool and Primary Scale of Intelligence-III Assessment, *MCAST* Manchester Child Attachment Story Task, *PERIK* Positive Development and Resilience in Daycare Center’s Daily Routine, *SDQ* Strengths and Difficulties Questionnaire, *SRS* Self-Reflective Functioning Scale.

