### Power analysis

The sample calculation and power analysis is based on α = 0.05 at a power of 0.80, using the pre/post differences of the mentioned FPS. We expect at least an effect size of *d* = 0.5. Further, if we used a RCT study design for analysis of variances, the minimum sample size would be *n* = 63 per treatment. In contrast, we applied a CRCT design with the daycare centers as given clusters. (Note: each daycare center represents one cluster.) We used a formula introduced by Eldridge *et al*. [45], providing a conservative estimate of sample size requirements for trials using cluster-level analyses weighted by cluster size.

$$n*=\left\{1+\left[\left(1+\mathrm{CV}2\right)\times m–1\right]\times \mathrm{ICC}\right\}\times n$$

The formula for the corrected sample size *n** consists of the coefficient of variation *CV* for trials with unequal cluster sizes (that means with unequal sizes of daycare centers) and the intra class correlation coefficient *ICC* within the clusters and the mean cluster size *m*. Using again the findings of the Frankfurt Prevention Study, the estimated coefficient of variation is *CV* = 0.467 and the estimated intra class correlation coefficient (based on the pre/post differences including the *CV*) *ICC* = 0.0465. We expect a mean cluster size *m* = 20 or at least *m* = 17 children. The corrected sample size for the first scenario would be *n** = 131.44 (if *m* = 20) divided by 20 = 6.57; in the second scenario *n**=120.73 (if *m* = 17) divided by 17 *n** = 7.10. For both scenarios, seven clusters, respectively seven daycare centers per treatment, should be selected.

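### As most naturally read, the main MCAST analysis is a change-score contrast; naming the t0 score as a fixed covariate would add precision at no cost in data

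*Protocol article*

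**What the plan says.** The section on the primary outcome (MCAST attachment representation) states that "the main analysis involves changes in MCAST disorganization and narrative coherence scores from the baseline and the endpoint", compared between the arms. For this, "an analysis of covariance is applied with repeated measures and linear regression with autocorrelated data (compound symmetric covariance structure models"). The same paragraph gives one rule for covariates, placed after the description of baseline characteristics and dropout: "Relevant characteristics will be added if applicable as covariates to the models". The t0 MCAST score is not mentioned as a covariate, and nothing says that the arms share a mean at baseline.

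The Assessments section shows that the t0 score is available: for the children, "assessment is conducted before (t0 pre) and after intervention (t2 post"), with a further follow-up a year later.

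The Power analysis section sizes the trial "using the pre/post differences of the mentioned FPS". It states: "The sample calculation and power analysis is based on α = 0.05 at a power of 0.80" and "We expect at least an effect size of *d* = 0.5". The ICC is also estimated on those differences.

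**The concern.** In a repeated-measures model with t0 and t2 as the two outcomes, arm means free at t0 and complete data, the arm-by-time term is exactly the difference between arms in mean change. That contrast fixes the slope on the baseline score at 1. Baseline adjustment estimates the slope from the data and so minimizes the residual variance. Unless the best slope happens to be 1, the change score carries extra noise, and it over-corrects when the arms differ at t0 by chance. Such differences are a practical possibility: the Randomization section describes allocating 14 centers from a table of random numbers and mentions no stratification at that step.

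At stake is the precision of the primary comparison in a trial with only seven centers per arm, where more centers are costly and the baseline score is already being collected.

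**Working it through.** **Inputs from the Power analysis section:** d = 0.5 on the pre/post difference, alpha 0.05 (two-sided reproduces the plan), power 0.80, CV = 0.467, ICC = 0.0465, m = 20 or 17, 7 centers per arm. **Not in the documents:** the pre/post correlation rho and the ratio of the t2 SD to the t0 SD. Both are assumptions here.

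**1. The plan's own figures.**
- Individual randomization: 2 × (1.960 + 0.842)² / 0.5² = 62.8, so 63. The plan says "the minimum sample size would be *n* = 63 per treatment".
- Design effect 1 + [(1 + CV²)m − 1] × ICC = 2.0863 (m = 20) or 1.9164 (m = 17).
- Times 63: 131.44 and 120.73, or 6.57 and 7.10 centers.

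All figures match the article.

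**2. Power of the change-score contrast with 7 centers per arm.** The effective n per arm is 7m / design effect = 140/2.0863 = 67.1 or 119/1.9164 = 62.1. The noncentrality is 0.5 × √(effective n / 2) = 2.90 or 2.79. Power is 0.825 / 0.796 (m = 20 / m = 17) by the normal approximation, which is the plan's method, and 0.758 / 0.725 with a t-test on 12 df for 14 centers.

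**3. Variance ratio.** Write k for the t2 SD divided by the t0 SD, with the t0 SD as unit.
- Change score: 1 + k² − 2·rho·k.
- Baseline-adjusted: k²(1 − rho²).
- With k = 1 the ratio, adjusted to change, is (1 − rho²) / [2(1 − rho)] = (1 + rho)/2.

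**4. Power with baseline adjustment**, for k = 1 and the same proportional reduction within and between centers (m = 20 / m = 17):

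| rho (assumed) | variance ratio | power, normal | gain, points | power, t on 12 df | gain, points |
|---|---|---|---|---|---|
| 0.3 | 0.65 | 0.949 / 0.933 | 12.3 / 13.7 | 0.909 / 0.887 | 15.1 / 16.1 |
| 0.5 | 0.75 | 0.917 / 0.896 | 9.1 / 10.0 | 0.866 / 0.839 | 10.8 / 11.4 |
| 0.7 | 0.85 | 0.881 / 0.856 | 5.6 / 6.0 | 0.822 / 0.792 | 6.4 / 6.7 |
| 0.8 | 0.90 | 0.863 / 0.836 | 3.7 / 4.0 | 0.800 / 0.769 | 4.2 / 4.4 |
| 0.9 | 0.95 | 0.844 / 0.816 | 1.9 / 2.0 | 0.779 / 0.747 | 2.1 / 2.2 |

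Spending one further degree of freedom (11 instead of 12) lowers the adjusted power by about 0.5 point.

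**5. If adjustment shrinks only the within-center part.** The design effect splits into 1 − ICC = 0.9535 within and (1 + CV²) × m × ICC = 1.1328 (m = 20) or 0.9629 (m = 17) between. At rho = 0.5 the variance factor is (0.75 × 0.9535 + 1.1328)/2.0863 = 0.886, or (0.75 × 0.9535 + 0.9629)/1.9164 = 0.876. Power on 12 df becomes 0.806 / 0.780, a gain of about 5 points. The corresponding gain is about 7 to 8 points at rho 0.3 and about 3 at rho 0.7.

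**6. If the t2 SD exceeds the t0 SD.** At rho = 0.7 and k = 1.4 the change-score variance is 1 + 1.96 − 1.96 = 1.00 and the adjusted variance is 1.96 × 0.51 = 0.9996. The best slope is rho × k = 0.98, and the gain all but disappears.

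**The case against.** The strongest objection is that the article names analysis of covariance, whose usual covariate in a pre/post trial is the baseline score. Analysis of covariance applied to change, with baseline as covariate, gives the same arm effect as when applied to the endpoint, so the word change settles nothing. MCAST is also measured at t3, so t2 and t3 could be the correlated outcomes with t0 as covariate. This stands in part: the text is mixed rather than clearly unadjusted. A reader might infer that the plan rules out baseline adjustment, and the documents do not support that. But the stated contrast runs from baseline to endpoint, the covariate rule is conditional and names nothing, and the power calculation uses differences. Together these make the change-score reading the most natural one.

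It can also be said that an article leaves model detail to an analysis plan. That is fair for what is unmentioned. Here, however, the contrast, the covariance structure and a covariate rule are all stated, and as stated they point to the less efficient estimator.

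A reader might infer a fixed loss of about 10 points. That figure needs rho near 0.5, which no document gives. The power inputs come from the earlier prevention study, whose results reported in the Background section concern aggressiveness, anxiety and hyperactivity, so they say nothing about the correlation or SDs of the MCAST scores.

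A reader might also infer that the trial is underpowered because of the change score. The documents do not support this either: d and the ICC already refer to differences, and the plan's arithmetic reproduces. The lower 0.758 / 0.725 comes from using 12 df, which is a separate matter. Nor is bias shown: under randomization the change-score contrast is unbiased.

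**Conclusion.** The point holds as one of efficiency and clarity. The described main analysis, as most naturally read, is a difference in mean change. Apart from a negligible df cost, that is never more precise than adjustment for the t0 score. The added power in the same 14 centers is about 12 to 16 points at rho 0.3, falling to about 2 at rho 0.9. Each range spans the two mean center sizes and the normal and 12-df calculations. It rests on equal variances at t0 and t2 and an equal proportional gain within and between centers. It is roughly halved if only within-center variance shrinks, and can nearly vanish if the t2 SD is sufficiently larger than the t0 SD. It is a gain available above what was planned, so the stated sample size needs no correction on this account.

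**What to change.** In the section on planned analyses for the primary outcome, state that the dependent variable is the t2 MCAST disorganization score (and, separately, the t2 narrative coherence score), with the child's own t0 value of that score as a prespecified covariate that is always included and does not fall under the conditional covariate rule. Alternatively, keep the repeated-measures model and constrain the two arms to a common mean at t0. Keep the allowance for center in either form. Report the adjusted arm difference at t2 as the effect, with mean changes as description only.

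The cost is wording: the t0 MCAST is already collected, and no further children or centers are needed. The one practical point to settle is a child without a usable t0 score, which the common-baseline model or a simple baseline imputation can handle.

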**Methods/Design:**

Preschoolers in 14 daycare centers in Frankfurt, Germany, participate in a cluster randomized controlled trial (CRCT). The daycare centers were randomly chosen from a representative baseline survey of all Frankfurt’s daycare centers carried out in 2003 (*n* = 5,300) with the following stratifying factors: children’s aggressiveness, hyperactivity, anxiety and socioeconomic status. Additionally, the geographic identification of socioeconomically deprived neighborhoods regarding low-income children was taken from the Frankfurt Municipality Statistics. Children’s attachment classification and children’s aggressiveness, hyperactivity, anxiety and social competence are measured as outcome criteria before and after 2 years of intervention. The programs in the study aim to reach a high-risk population. Therefore, the combination of a random sampling of daycare centers out of a representative baseline survey in all daycare centers in Frankfurt and the application of official data on the local distribution of low-income children are unique features offered by the EVA study design. Data on preschooler’s attachment representations are collected in socioeconomically deprived neighborhoods for the first time.

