### Outcome

The primary measure of outcome, the Manchester Child Attachment Story Task (MCAST) [42], seems to be a promising approach to evaluate results beyond the well established cognitive measures and questionnaires. Attachment representations are found to be crucial moderators for child development [43], highlighting the importance of parenting practices for children with low-SES status [4,43,44]. Therefore, the intervention response is defined as the change from children’s insecure attachment representation to a more secure one. Within the insecure attachment representations, intervention response is also defined as the change towards a more structured attachment representation (that is, statistically significant change in the disorganization score and the narrative coherence score, Likert scale, range 1 to 9).

Second outcome measures include the German adaptation of HAWIVA [41], the C-TRF [33,34], the SDQ [35,36] from the teacher’s and parent’s perspective, and the PERIK [37,38].

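### Cox regression and log-rank tests do not suit attachment classification, a reversible state seen only at 0, 24 and 36 months; a cluster-adjusted categorical model with tabulated transitions fits better

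*Protocol article*

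**What the plan says.** Under Planned analyses for the primary outcome, the article names two families of methods for the four-class MCAST result: "Changes in the overall attachment classifications are calculated by tests for frequency distributions and procedures of survival analysis (Cox, regression, log-rank tests". The same section makes change in the disorganization and narrative coherence scores the main analysis.

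The Assessments section fixes when the MCAST is given: "Children’s assessment is conducted before (t0 pre) and after intervention (t2 post), as well as 1 year after the end of intervention (t3 follow-up". Table 2 dates these visits as "t2 (post study, 24 months" and "t3 (follow-up, 36 months" and lists no child measure at 12 months. The abstract describes attachment and behavior as outcomes that "are measured as outcome criteria before and after 2 years of intervention".

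The Outcome section sets the direction of response: "the intervention response is defined as the change from children’s insecure attachment representation to a more secure one". For children who stay insecure, it adds movement towards a more structured representation.

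**The concern.** Survival methods compare when events happen. Here the date of a change is never observed. It is known only that the class differed between one visit and the next, and those visits are 24 and then 12 months apart. Attachment class is also a state that a child can enter and leave, not a once-only event.

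Three things are at stake. A hazard ratio reported for this component would depend on a software setting. The log-rank p-value would look like a second test but carry no new information over the 2-year window. And with response defined in one direction, an analysis restricted to response gives initially secure children no way to count, so their worsening would not appear in it.

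**Working it through.** **The plan's own figures.** The article gives no hazard ratio, event rate or event count, so there is no survival calculation to reproduce. The sample size rests on a difference in means and does reproduce. The design effect is 1 + [(1 + 0.467²) × m − 1] × 0.0465, which is 2.0863 for m = 20 and 1.9164 for m = 17. Multiplied by 63 this gives 131.44 and 120.73, as stated. It does not depend on the point below.

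All response rates and group sizes from here on are assumptions for illustration. Clustering is ignored, to isolate the effect of the method.

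**1. Log-rank with one post-baseline visit.** Assume 60 insecure children per arm, with 24 (40%) and 15 (25%) responding at 24 months. All 39 events share one time.
- Observed minus expected in the first arm: 24 − 39 × 60/120 = 4.5.
- Variance: 39 × 0.5 × 0.5 × (120 − 39)/(120 − 1) = 6.637.
- Log-rank chi-square: 4.5²/6.637 = 3.051.
- Pearson chi-square: 120 × (24 × 45 − 15 × 36)²/(39 × 81 × 60 × 60) = 3.077.
- Relation: 3.077 × 119/120 = 3.051.

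The log-rank statistic is Pearson × (N − 1)/N. With an assumed 84 per arm and 30% v 50%, the pair is 7.132 and 7.175.

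**2. Cox with one post-baseline visit, same 24/60 v 15/60.**

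| Tie handling | Hazard ratio | Wald p |
|---|---|---|
| Breslow | 0.40/0.25 = 1.60 | 0.153 |
| Efron | 1.76 | 0.087 |
| Discrete (conditional) | 1.99 | – |

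The Breslow value is the risk ratio. The discrete value is close to the odds ratio, (0.40/0.60)/(0.25/0.75) = 2.00. For comparison, the grouped-time hazard ratio, from a separate complementary log-log model, is ln 0.60/ln 0.75 = 1.78.

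**3. Adding the 36-month visit.** Assume 80 per arm and 40 responders in each by month 36, split 32 + 8 in one arm and 16 + 24 in the other.
- Month 24: observed − expected = 32 − 24 = 8; variance 48 × 0.25 × 112/159 = 8.453.
- Month 36, with 48 and 64 still at risk: 8 − 32 × 48/112 = −5.714; variance 32 × (48/112) × (64/112) × 80/111 = 5.648.
- Log-rank chi-square: (8 − 5.714)²/(8.453 + 5.648) = 0.37, against 0.00 for the 36-month table.

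So the second visit adds some timing information, in two intervals. In a first-event analysis, however, a child who is secure at 24 months and insecure at 36 months remains a success.

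**4. One-directional response.** Assume 7 × 17 = 119 children per arm, 71 insecure and 48 secure at baseline.
- Insecure children who improve: 28/71 v 14/71, chi-square 6.63, p = 0.010.
- Secure children who worsen: 20/48 v 6/48.
- Secure at 24 months: 48 − 20 + 28 = 56 v 48 − 6 + 14 = 56.

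The response analysis shows a benefit although both arms end with the same number of secure children.

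**The case against.** A reader might infer that the schedule holds no time-to-event information at all. That is true from baseline to 24 months, but not once 36 months is used: two ordered intervals support a discrete-time analysis, and step 3 shows that timing can alter the result.

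A reader might also infer that the plan ignores children who deteriorate. It does not. The one-directional wording belongs to the response definition in the Outcome section and matches the third hypothesis, which concerns insecure children. The main analysis uses scores that move both ways, and frequency tests on four classes can show worsening. The gap lies only in an analysis of response taken alone.

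It can further be said that the log-rank test is not invalid, since with one visit it nearly equals Pearson's test and offers no real choice of p-values. The Cox values in step 2 partly reflect different effect measures, and Efron's 1.76 is close to the grouped-time 1.78. All of this stands. It does not make a Cox estimate interpretable when the tie option is unknown and moves it from 1.60 to about 2.0.

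Loss before 24 months is no argument against survival methods in particular: those children also lack the outcome in a categorical model.

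Finally, tie handling and event definition may be left to an analysis plan, and their absence here is no fault. But the choice of Cox and log-rank and the visit schedule are both stated in the article, and the mismatch is between those two.

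**Conclusion.** The point holds as a moderate one. Standard Cox and log-rank procedures suit a reversible state observed at one or two fixed follow-up visits poorly. In the 2-year window the log-rank test duplicates the frequency test by a factor of (N − 1)/N, and the hazard ratio runs from 1.60 to about 2.0 on the same assumed data. With 36 months added, reversion is hidden in a first-event analysis. Response alone can suggest a benefit where the net number of secure children is equal.

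The algebra in steps 1 and 2 holds for any single-visit data; the sizes rest on the assumed rates and numbers. It would go too far to conclude that the trial's main inference is at risk. The defect affects the classification component of the primary outcome, not the score-change main analysis and not the sample size.

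**What to change.** In Planned analyses for the primary outcome, delete standard Cox regression and log-rank tests. Replace them with one cluster-adjusted model of MCAST classification at 24 months in all children, conditional on baseline class: binary, ordinal or multinomial, fitted as a mixed model or as GEE with a small-sample correction, with daycare center as the cluster. An ordinal or multinomial form avoids collapsing the four classes. Make 36 months secondary and, if timing across the two visits is of interest, use a discrete-time model for it. Tabulate baseline-to-24-month transitions among the four classes by arm, so that worsening is visible beside response.

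The cost is a change of wording; no further data are needed, and the article reports recruitment as ongoing. If no discrete-time model is kept, the coarse timing across 24 and 36 months is lost.
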